## Abstract

**Background**: Prolonged sedentary behavior and associated obesity are recognized risk factors for poor health across the lifespan. Globally, data show that many children and adolescents aged 5 to 17 significantly increased their sedentary behaviors during the COVID-19 pandemic, failing to meet recommended physical activity levels and reporting increased smartphone use. While mobile devices and video games have been traditionally linked to physical inactivity, formats like exergaming, which combine gameplay with gross motor activity, offer potential to promote physical activity. However, many digital health tools for children are developed without incorporating feedback from key stakeholders and end-users (e.g., children, teachers, and guardians). Therefore, this paper, within the Walk around the Earth (E-Walk) project, describes a prospective study that aims (1) to identify the most influential factors or characteristics affecting engagement with and usability of a mobile application promoting physical activity among primary school students; (2) to develop a mobile application for children based on the identified factors and characteristics. **Methods**: This project will use a group concept mapping approach to identify the most influential features/factors/characteristics affecting engagement with and usability of an app. By involving primary stakeholders (e.g., children, teachers, guardians, and physical activity experts), the project seeks to align the app’s features with primary end-user needs and motivations. Following the app’s development, its effectiveness in increasing physical activity levels and reducing sedentary behaviors will be evaluated through a mixed-method design, incorporating anthropometric data, validated physical activity questionnaires (Physical Activity Questionnaire for Older Children (PAQ-C) and International Physical Activity Questionnaire (IPAQ)), and engagement metrics. **Conclusions**: The E-Walk project integrates participatory design with educational content and activity-based challenges, representing a multidimensional strategy for promoting health and learning in primary school students. Ultimately, this study contributes to the development of user-informed digital interventions that support sustainable behavioral changes, in line with broader goals of child well-being and digital health promotion.

## 1. Introduction

The prevention of non-communicable diseases, such as obesity and cardiovascular and metabolic conditions, particularly among children, is a major public health goal worldwide [1]. Global data show that many children and adolescents aged 5 to 17 years do not meet the recommended daily levels of physical activity, increasing their risk of overweight and obesity [2,3,4]. In 2022, more than 390 million children and adolescents were classified as overweight, with approximately 8% living with obesity [5], making childhood obesity one of the most serious public health challenges of the 21st century. The Organization for Economic Co-operation and Development/European Union document [6] confirmed the widespread prevalence of inadequate daily levels of exercise among children and adolescents, with important implications for national health systems. The COVID-19 pandemic further aggravated these trends, as digital home-based training was effective for adults [7], whereas children showed increased sedentary behaviors and screen exposure during lockdowns [8]. Several studies [9,10] reported a strong association between excessive screen time, particularly smartphone and tablet use, and sedentary lifestyles. Currently, 74% of European children aged between 7 and 12 years, and 83% of adolescents aged between 13 and 15 years report regular smartphone use, highlighting the widespread integration of digital devices into daily life [11].

Smartphones and tablets, including the software applications that run on these devices, have become an integral part of children’s lives, with substantial increases in usage in recent years [11], and it is unclear whether the (ab)use of such devices can actually be considered as part of “addictive” behavior [12]. While media such as video games have traditionally been associated with inactivity, new forms that combine play with motor activity (active video games or exergaming) may support children in meeting physical activity recommendations [13]. In parallel, a variety of mobile health and fitness apps have emerged, providing behavioral interventions to large population groups. Despite their potential, a critical limitation persists. Many strategies are developed without the involvement of thorough stakeholder feedback. In particular, the perspectives of children, who are the primary end-users, and teachers, who implement these programs within constrained classroom contexts, are often not adequately considered. This lack of participatory design reduces effectiveness, sustainability, and applicability of such interventions. Without a clear understanding of teachers’ challenges and children’s preferences and motivations, many initiatives risk being poorly aligned with their target users, limiting their impact on sedentary behavior reduction.

Nevertheless, previous digital interventions have yielded mixed results. While some school-based programs were able to increase physical activity in the short term, their effects often diminished over time without sustained engagement or contextual support [14]. Moreover, tools developed without active user involvement have frequently reported poor usability and limited integration into school routines [15]. These shortcomings highlight the need for participatory approaches that move beyond top-down designs. A promising strategy to address these challenges is group concept mapping, which offers a structured approach to integrating the perspectives of children, teachers, and stakeholders, thereby aligning more closely with real-world needs and strengthening its potential for long-term effectiveness and transferability [16].

Group concept mapping is a structured participatory methodology that systematically collects, integrates, and visually represents stakeholders’ perspectives [17]. By combing qualitative and quantitative methods [18,19,20,21,22,23], it enables the identification and prioritization of features that influence the usability of and engagement with health interventions [24]. Previous research supports that applying concept mapping in youth contexts [25] can reveal children’s genuine motivators (e.g., playful route expansions, scoreboard rivalry, cross-curricular quizzes) while also clarifying teacher concerns (e.g., limited time, alignment with academic schedules).

Given the increasing integration of smartphones and tablets into children’s daily routines, and the growing use of mobile applications for health promotion, it is essential to identify the features that make these tools engaging, accessible, and useful. Group concept mapping provides a structured way to achieve this by systematically incorporating the perspectives of primary school students, teachers, physical activity stakeholders, and families.

Within the Walk around the Earth (E-Walk) project [26,27], this participatory approach will first aim to identify the most influential factors affecting engagement with and usability of a mobile application designed to support physical activity in primary school students. Based on these insights, the project will then develop and refine a step-based app integrating educational and physical activity content, and subsequently evaluate its impact on (i) physical activity metrics (e.g., daily steps, minutes of activity), (ii) anthropometric parameters such as Body Mass Index (BMI), and (iii) changes in physical activity classification. Overall, the project seeks to address one of today’s most pressing health challenges by developing an intervention that combines physical activity, digital technologies, and learning opportunities, thus making physical activity more engaging and enjoyable.

## 2. Materials and Methods

### 2.1. Ethical Approval and Experimental Approach to the Problem

The E-Walk project obtained ethical approval from the Institutional Review Board of the Department of Human Sciences, Society and Health at the University of Cassino and Lazio Meridionale (Approval No.: 19764, dated 16 July 2025). To establish a comprehensive European framework of physical inactivity among children aged 9 to 15 years, the project will adopt an ethnographic approach integrated with concept mapping. This design will allow the exploration of children’s relationships with mobile apps, together with the perceptions of both students and teachers from diverse countries and contexts. By combining real-world insights with scientific expertise, this study aligns with an obligation–opportunity conceptual model.

Given the relatively broad age range (9 to 15 years), potential differences in motivations, developmental stages, and physical activity behaviors will be acknowledged and accounted for in the analyses by including age as a covariate or stratifying results by age group. The study primarily focuses on the design and development stages through group concept mapping, with the subsequent evaluation phase planned as a quasi-experimental pre-post study to assess the app’s impact on physical activity and sedentary behaviors.

### 2.2. Participants and Inclusion/Exclusion Criteria

Participants will include primary school students aged 9 to 15, schoolteachers, physical activity stakeholders, and relatives or guardians. Students will be subsequently divided into two age groups (9 to 12 and 13 to 15). Inclusion will be restricted to those regularly enrolled in primary schools and able to read and understand the language of the validated questionnaires used in each country. Only children with access to a compatible mobile device, either personal or shared, will be admitted. Those with medical conditions or physical disabilities that contraindicate moderate-to-vigorous physical activity, or with cognitive or developmental impairments that prevent them from comprehending the app content or questionnaire items, will not be eligible.

Teachers will be eligible if employed at one of the participating schools or directly involved in school activities. They must be able to complete the questionnaires and engage with app-related tasks, possessing sufficient digital literacy to use a smartphone or tablet. Adults with severe health conditions preventing participation in physical activity or those unable to engage with digital tools will be excluded.

Parents, guardians, and other stakeholders will be included if directly involved in supporting children’s education or physical activity and available to participate in focus groups, surveys, or feedback activities related to the intervention. Those lacking sufficient access to digital devices and literacy to engage with the app-based activities will be excluded.

Recruitment will take place through workshops organized in one or more local schools, ensuring a diverse range of ages and socio-cultural backgrounds. Participation will be voluntary, and all participants will be fully informed about the project and its aims. They will be allowed to withdraw from the study at any time without consequences. Written informed consent will be obtained from the participants. For children, written parental consent will also be required. In accordance with Regulation (EU) 2016/679 of the European Parliament and Council on the protection of personal data (General Data Protection Regulation), each participant will be assigned an anonymous identification code. All collected data will be used exclusively for statistical and research purposes.

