In line with the study’s objectives, specific success indicators will be used to evaluate the impact of the intervention. Primary indicators will include changes in physical activity metrics such as daily step count, minutes of moderate-to-vigorous activity, and reductions in sedentary time, as recorded through app-based measures and validated questionnaires. Physical activity levels will be assessed using the Physical Activity Questionnaire for Older Children (PAQ-C) [31] for children (students aged 9–15 years) and the short version of the International Physical Activity Questionnaire (IPAQ) [32] for teachers (adults aged ≥ 18 years old). The PAQ-C is a self-administered tool for children, providing a score from 1 (low activity) to 5 (high activity) based on nine items. The tenth item, related to illness, is not included in the final score. The PAQ-C has been validated in different countries and cultural contexts, demonstrating good reliability for assessing self-reported physical activity among school-aged children [31]. It has been translated into multiple languages and adapted to local habits (e.g., types of common sports or leisure-time activities), which makes it suitable for use in our multinational study context. The IPAQ includes 7 items assessing frequency, intensity, and duration of physical activity, along with sitting time. It includes both categorical (inactive, minimally active, HEPA active) and continuous scores (MET-minutes/week) [33,34]. The IPAQ has been validated for adults in more than 20 countries, with standardized translations and cultural adaptations [32]. In addition, anthropometric parameters will be collected as complementary success indicators to monitor changes in body composition and overall health status during the project. Weight and height will be determined using a precision instrument that combines a scale and stadiometer accurate to 0.1 kg and 0.1 cm (Seca, model 709, Vogel & Halke, Hamburg, Germany). Additionally, the BMI will be calculated. Both physical activity levels and anthropometric data will be evaluated for the entire three-year duration of the project.

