#### 2.5.2. Planned Mobile App Architecture and Functionalities

To address transparency regarding the technical and functional design of the E-Walk app, a dedicated description of the app’s planned architecture is provided below. While the app is still under development, the design roadmap and anticipated features are outlined to ensure clarity and reproducibility. The E-Walk application will be developed as a cross-platform native app using interface development technologies that ensure compatibility with both Android and iOS devices. Data storage and backend functionalities will rely on a platform providing secure, cloud-based management of activity metrics, user profiles, and educational content. This architecture enables real-time data synchronization, offline use, and scalable data handling. The key functionalities will be as follows:Physical activity tracking: Integration of GPS tracking and step counters to record activity duration, distance, and intensity. Data will be complemented by user-reported activity logs.Educational modules: short interactive quizzes and mini-games designed to stimulate cognitive engagement, aligned with topics identified through concept mapping.User interaction modes: options for individual challenges and team-based competitions, allowing flexible engagement and promoting social motivation.Feedback collection: in-app surveys, ratings, and motivational prompts to capture user enjoyment, preferences, and suggestions.Gamification elements: points, badges, and leaderboards to reinforce engagement and reward consistent participation.

All collected data will be anonymized and securely stored on the Firebase platform, with strict adherence to data protection regulations. Parents and teachers will have access to summarized reports of physical activity and educational engagement.

The app will follow an iterative development process:Prototype phase: initial interface and feature mockups tested with a small sample of children and teachers.Pilot testing: functional beta version deployed to evaluate usability, data collection accuracy, and engagement.Full deployment: iterative refinement based on pilot feedback, including scaling educational content and activity tracking features.

This structured design ensures that the E-Walk mobile application will be robust, user-friendly, and aligned with the needs and expectations of primary school students.

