## 5. Limitations

This research design has some limitations that should be considered when interpreting its aims and potential outcomes. The reliance on self-report questionnaires (PAQ-C and IPAQ), while validated and widely used, may be affected by recall errors and social desirability bias, and participant recruitment could be subject to selection bias, as schools and families already interested in health promotion may be more likely to participate. The heterogeneity of the target age group (9–15 years) represents an additional challenge, since developmental differences can influence both the usability of the mobile app and children’s engagement. The project also depends on technological availability, which raises the risk of a digital divide, while variability in school resources and teachers’ workload may affect feasibility and consistency across contexts. Moreover, as highlighted by the literature [12] where digital health tools produced neutral or limited effects, maintaining user motivation and ensuring long-term sustainability are recognized difficulties. To mitigate these issues, the E-Walk project adopts a participatory group concept mapping approach to align the intervention with children’s, teachers’, and families’ perspectives, integrates objective indicators such as anthropometric and app-based engagement metrics to complement self-reports, and embeds educational and gamified elements to enhance adherence over time. These strategies are expected to reduce contextual barriers and increase the effectiveness and sustainability of the intervention compared with similar initiatives.

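### For children, daily steps and minutes of moderate-to-vigorous activity come only from an app on phones that may be shared, so changes in carrying or sharing cannot be told from changes in activity

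*Protocol article*

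**What the plan says.** All references are to the protocol article.

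- **Eligibility (section 2.2).** A shared device is enough: "Only children with access to a compatible mobile device, either personal or shared, will be admitted".
- **Primary indicators (section 2.5).** "Primary indicators will include changes in physical activity metrics such as daily step count, minutes of moderate-to-vigorous activity, and reductions in sedentary time", and these are to be taken "as recorded through app-based measures and validated questionnaires".
- **Children's questionnaire (section 2.5).** "The PAQ-C is a self-administered tool for children, providing a score from 1 (low activity) to 5 (high activity) based on nine items". The other questionnaire, the IPAQ, covers duration of activity and sitting time but is assigned to teachers.
- **App measurement (section 2.5.2).** Activity is recorded by GPS and step counter, and no separate wearable is named. The text adds: "Data will be complemented by user-reported activity logs". The same app carries "points, badges, and leaderboards to reinforce engagement and reward consistent participation".
- **App development (section 2.5.2).** Full deployment involves refinement in the light of the pilot, "including scaling educational content and activity tracking features".
- **Design (sections 2.1 and 2.6).** The evaluation is a non-randomised before-and-after comparison, with follow-up at, for example, 6 and 12 months. No control group is described.
- **Limitations (section 5).** Recall error and social desirability are attached to the two questionnaires. Among the mitigations, the project "integrates objective indicators such as anthropometric and app-based engagement metrics to complement self-reports".

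**The concern.** The intervention is also the measuring instrument. An app that succeeds in getting children to use their phones more may change how long they carry them, and so change the step count, without any change in how much they walk. On a shared phone the count also includes the steps of other users.

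A concurrent control group using the same recording method could show part of this drift. With only a before-and-after contrast, the drift is absorbed into the estimated effect. Two of the three indicators named as primary are exposed.

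Section 5 then steers the reader the wrong way. It treats bias as a problem of the questionnaires and offers app-based metrics as part of the remedy.

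**Working it through.** The article gives no figure on this point to reproduce: no carried share, no proportion of shared devices and no expected change in steps. The check is therefore a comparison of the passages, followed by an illustration.

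**Step 1. Where can each indicator come from, for a child?**

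- Daily steps: the app's step counter can supply them. The PAQ-C, as described, gives a score from 1 to 5, which is not a step count.
- MVPA minutes: the app can supply them through duration and intensity. The PAQ-C score is not in minutes. The IPAQ records duration but is for adults.

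So although section 2.5 names two kinds of source, only the app is described as able to deliver these two indicators in children.

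**Step 2. What does the phone record?** Let T be the child's true daily steps, p the share of them taken while carrying the phone, and O the steps added by any other user. Then

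R = p × T + O.

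R equals T only if p = 1 and O = 0. A comparison over time is distorted if p or O changes.

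**Step 3. Carrying alone** (T constant, O = 0). Recorded change = p(after) / p(before) − 1. The values of p are assumptions.

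- 30% to 45%: 0.45/0.30 − 1 = +50%
- 40% to 50%: 0.50/0.40 − 1 = +25%
- 50% to 60%: 0.60/0.50 − 1 = +20%
- 60% to 66%: 0.66/0.60 − 1 = +10%
- 50% to 40%, if use wanes: 0.40/0.50 − 1 = −20%

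**Step 4. Sharing alone** (p × T constant and set to 1; O assumed between 0 and 0.30 of it).

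- O from 0 to 0.10: 1.10/1.00 − 1 = +10%
- O from 0 to 0.30: 1.30/1.00 − 1 = +30%
- O from 0.30 to 0: 1.00/1.30 − 1 = −23%
- O stable at 0.30 with an assumed true rise of 10%: (1.10 + 0.30)/1.30 − 1 = +7.7%, so a real change is diluted

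The sign can go either way.

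**Step 5. Is there a value from before the app?** Section 2.3 lists questionnaires and anthropometry as the baseline measures. Section 2.6 adds app usage and engagement metrics to a baseline that precedes implementation of the app. Neither names a baseline step count. The two sections need to be reconciled, because without a value from before the app the step comparison has no clear starting point.

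**Step 6. Does section 5 cover this?** It does not mention carrying, sharing or attribution of steps. Engagement metrics measure use of the app, which is not activity. The logs that complement the sensor data are themselves self-report. Anthropometry is objective, but it does not measure activity.

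**The case against.** The strongest reply is that much of this is still open or sits elsewhere. Section 2.5.1 leaves the app metrics to be defined by the concept mapping. The pilot in section 2.5.2 is to assess how accurately data are collected. Section 2.6 sends the analysis to Supplementary File S1, which is not at hand. Rules on valid days, minimum carrying time or attribution may be there. That stands: their absence from the article is not counted as an error. Device eligibility, the complementing of sensor data by logs and the wording of section 5 are, however, stated in the article itself.

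It can also be said that section 5 speaks of engagement metrics rather than step counts, and that section 2.3 treats app usage as a process measure. That is fair, but it does not rescue the sentence: a measure of app use cannot offset bias in self-reported activity.

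Several stronger readings are tempting and are not supported:

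- **Logs are added to the step count, or log entries earn points.** The text says only that the data are complemented by logs and that rewards go to consistent participation.
- **Steps are the sole primary outcome.** They are one named example among several, and the PAQ-C does not depend on a phone.
- **The count has nothing to do with the child's activity.** It would be a biased and contaminated measure of it, not an unrelated one.
- **Tracking code will change between visits.** The text describes refinement following the pilot and does not place it between baseline and 12 months. Nor does it rule this out.
- **All the errors favour the app.** Stable sharing need not change over time, and waning use would push the count down. The introduction and section 5 both acknowledge fading engagement.

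**Conclusion.** The point holds in this form. For children, two of the primary indicators have no described source but an app on a phone that may be shared, in a design that cannot separate a change in carrying or sharing from a change in activity. Section 5 does not disclose this and presents app engagement metrics as an objective remedy.

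The direction and size of the bias are unknown. Under assumed carried shares, the recorded change ranges from −20% to +50% with true steps unchanged. The 40% to 50% case gives +25%. These figures show that the bias is possible, not how large it will be here. The conclusion rests on the article's description of the PAQ-C and the app, and on no wearable or other step source being specified in documents not shown.

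The change should be made now, while the app is still in development. The PAQ-C analysis is not affected.

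**What to change.** 1. **Device type.** Record personal or shared device at enrolment. Keep all children in the main step and MVPA analysis, and repeat it in those with a personal device as a sensitivity analysis. It should not be the sole analysis: restricting to device owners would select on ownership and aggravate the digital divide that section 5 already names.
2. **Logs.** Hold user-reported logs as a separate variable, outside the sensor-based step and MVPA outcomes.
3. **Tracking version.** Finish refining the tracking features before baseline and keep the version fixed through 12 months. Failing that, record the version in force for each child's data. Educational content can still be updated.
4. **Section 5.** State that app metrics depend on phone carrying, sharing and app use, and stop offering engagement metrics as objective mitigation of self-report bias.

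The cost is one extra enrolment field, a smaller sample in the sensitivity analysis and less freedom to update tracking. None of this removes the bias from changed carrying. It makes the part due to sharing and software visible and has the rest stated openly.
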